**Abstract**

**Background:**

Alcohol consumption is a major health problem worldwide. It affects all systems of the body especially the gastrointestinal tract. Acute or chronic alcohol consumption has deleterious effects on the gastrointestinal mucosa vary from increased intestinal permeability, structural changes to sever destruction of the epithelial lining cells. Human data are still limited and most of the studies were performed in chronic alcohol abusers.

We hypothesize that moderate alcohol drinking also may increase small intestinal permeability and contribute to the subsequent disruption of the tight junction complex. This study may provide more insight into the effects of moderate alcohol drinking on the small intestinal permeability.

**Aims of the study:**

The study aims to investigate the effects of moderate ethanol drinking on the intestinal permeability and the tight junction complex. If there is increase in the intestinal permeability, these effects will be investigated at molecular level.

**Study design:**

The study is designed as a placebo-controlled crossover trial.

**Study populations:**

For the study, volunteers who signed the informed consent form, males, between 18 - 45 years old, physically fit, without liver disease, of Caucasian ethnicity and of normal body weight will participate in the study.

**Interventions:**

During this study, alcohol will be administered intraduodenally to induce changes in the intestinal permeability. The exact dose of ethanol will be determined in the explorative study.

**Primary outcome of the study:**

The primary outcome is to assess the small intestinal permeability by means of sugar permeability testing after intraduodenal administration of ethanol.

**Secondary outcomes of the study:**

The secondary outcomes are to assess tight junction’s structure in the biopsy specimens, to examine effects of ethanol and acetaldehyde on mucosal permeability in biopsy specimens in *ex vivo* circumstances using Ussing chamber methodology and to measure serum and mucosal ethanol and acetaldehyde concentrations.

**Risks associated with participation:**

The possible risks in the study are related to the effects of ethanol on the nervous system such nausea, vomiting and euphoria. There are also possible risks related to the intervention with the gastroduodenoscope e.g. the risks of bleeding at the site of the biopsy and perforation of the viscera.

**Introduction**

Alcohol consumption leads to major health problems worldwide1. Especially chronic alcohol consumption has health and social consequences and may lead to dependence as well as other medical problems such as acute and chronic liver disease, acute and chronic pancreatitis, diabetes and ischemic heart diseases1. The average amount of alcohol consumed and the drinking patterns vary between geographical areas. The mean consumption of alcohol is highest in Europe and Northern America, and lowest in the Eastern Mediterranean1. According to estimates of the World Health Organization (WHO), about two billion people worldwide consume alcoholic drinks on a regular basis. In 2000, the global level of alcohol consumption was estimated to be approximately 5.8 liters of pure alcohol per capita per year1.

Most people associate moderate alcohol intake with cardiovascular health benefits, but do not consider the fact that it may increase the risk of gastrointestinal malignancies and alcoholic liver disease (ALD)1. Animal and in vitro studies have shown that alcohol can increase the intestinal permeability2, 3. Subsequently, also Rao *et al*.4 reported that chronic alcohol intake increased intestinal permeability, followed by an excessive influx of endotoxin and bacteria and consequently the risk of liver injury , which might be a crucial element in the development of ALD5. These findings suggest that alcohol leads to an increased intestinal permeability, thereby contributing to the development of ALD.

Intestinal permeability is an indicator for the intestinal barrier function, which regulates the passage of molecules down a concentration gradient6. There are two different routes for permeation, namely the transcellular route, which allows permeation across cells and the paracellular route, which allows permeation between cells. The latter route is regulated by tight junctions (TJs) between the epithelial cells of the intestinal mucosa (Figure 1)7. TJs appear as a network of sealing strands and act as a physical intercellular barrier that controls paracellular transport and restricts the movement of lipids and proteins between the apical and basolateral domains of the cellular membrane4***.*** TJs are composed of several transmembrane proteins namely, claudins, the integral membrane proteins occludin and junction adhesion molecules (JAMs). Another group of proteins are located at the cytoplasmic side, the zona occludens i.e. ZO-1, ZO-2 and ZO-3 proteins. It has been suggested that, ZO- proteins have a crucial role in junction formation 8, they connect between the TJ complex and the actin cytoskeleton8.

Opening of the TJs is regulated through a series of signal transduction pathways, resulting in the increased activity of the myosin light chain kinase (MLCK), which phosphorylates myosin and causes contraction of the cytoskeletal components and conformational changes in the associated structures, the tight junctions9-11.

**Figure 1: Structure of the tight junction complex.** Van Itallie, Physiology, 2004 7

Different molecules, such as glucose, amino acids11, 12, capsaicin13 and probably also alcohol8 are able to induce opening of the TJs and thereby increase paracellular permeability.

After ingestion of alcoholic drinks, the ethanol contained within can be present throughout the gastrointestinal tract (GIT). About 20% is absorbed in the stomach and about 75% is absorbed in the small intestine, by simple diffusion14-17.

A small amount of alcohol is absorbed and metabolized locally in the oral cavity by microbiota as well as in the oesophagus18. In case of ingesting a single high dose of ethanol (1.5 g/kg of body weight), equal levels can be measured in the lumen of the ileum and colon compared to the blood, as ethanol reaches the ileum and colon by diffusion from the vascular space14, 19.

Once absorbed in the stomach and intestine, ethanol passes into the portal vein to the liver, the main site responsible for metabolizing ethanol. There are also many extra-hepatic sites capable of metabolizing ethanol, namely stomach, lung and colon19. In the colon, small amounts of ethanol are metabolized by the colonic bacteria19.

In the liver and to a lesser extent in other organs (i.e. Stomach), ethanol is oxidized to acetaldehyde and finally into acetate, which are defined as the hepatic and gastric first-pass metabolism (FPM) , respectively20. In the liver, there are three metabolic pathways with different capacities for oxidizing ethanol, namely, alcohol dehydrogenase (ADH), the microsomal ethanol oxidizing system (MEOS) and catalase. All these pathways oxidize ethanol to acetaldehyde20.

Alcohol dehydrogenase pathway is the major pathway capable of oxidizing ethanol in the liver16. It involves the cytosolic enzyme alcohol dehydrogenase (ADH)16. In human, five classes of ADH have been discovered, class I-V21. Class I has many isoenzymes with different metabolic capacities present in the liver, stomach and the lung18, 20.

The microsomal ethanol oxidizing system (MEOS), which uses the cytochrome P450 system (CYP2E1) enzyme22 is predominantly present in the microsomes of the hepatocytes and induced by chronic alcohol consumption and high concentrations of ethanol (*K*m = 8 to 10 mM, compared with 0.2 to 2.0 mM for hepatic ADH)20. Comparable to ADH, CYP2E1 oxidizes ethanol and generates acetaldehyde.

The catalase pathway, located in the peroxisomes is capable of oxidizing ethanol in the presence of hydrogen peroxide (H2O2)20, but is considered only a minor pathway of ethanol oxidation23.

The end-product of these pathways, acetaldehyde is oxidized to acetate through the action of the enzyme aldehyde dehydrogenase (ALDH), which is localized in mitochondria ( Figure 2 )14, 20.

**Catalase pathway**

**ADH pathway**

**MEOS pathway**

**Figure 2: Ethanol metabolism.** Zakhari, S., Alcohol Res Health,2006 20

As described previously, the intestinal barrier is provided by intact tight junction complex. Disruption of the tight junctions leads to an increase in intestinal permeability, which can be caused by several nutritional and injurious agents, including ethanol4. Several researchers have investigated effects of ethanol on intestinal permeability, using cell lines or animal models but very few data exist on the human in vivo situation. In vitro and animal data revealed different effects of ethanol, varying from no detectable change in permeability24 to an increase in permeability3. The exact mechanisms through which ethanol may lead to an increase in intestinal permeability are not fully understood. Ma *et al*.8 showed that ethanol in low non-cytotoxic doses can lead to disruption of the Caco-2 cell tight junction barrier, most likely mediated by activation of myosin light chain kinase (MLCK)8. In addition, ethanol also stimulates MLCK-activity, but without affecting MLCK-protein levels8. The opening of the tight junctions is a functional and reversible process8. On the other hand, several investigators24-27 concluded that the cytotoxic and carcinogenic metabolite, acetaldehyde can disrupt the tight junctions in Caco-2 cell monolayer. This disruption is caused by induction of tyrosine phosphorylation24-27.

Rao *et al*.24 compared the effects of both ethanol and acetaldehyde on intestinal permeability in Caco-2 cell lines. They concluded that acetaldehyde but not ethanol did result in an increased permeability, measured by transepithelial electrical resistance (TEER), sodium chloride dilution and the unidirectional mannitol flux24.

Reliable data from human studies on the effect of ethanol on intestinal permeability are scarse5, 28-33. In most cases, the experiments have been performed after chronic alcohol abuse in alcohol addicts5, 29, 31. Robinson and co-workers concluded that ethanol can induce a transient increase in intestinal permeability using polyethylene glycol 400 (PEG-400). This effect resolved within one day in healthy volunteers after a single high dose of alcohol and within four days in chronic alcoholics33. Bjarnason *et al*.28 used chromium-51 labelled ethylenediamine tetra acetic acid (51Cr-EDTA) as a permeability marker and found that chronic alcohol consumption lead to an increase in intestinal permeability in alcoholic patients28 . Parlesak *et al* 32 investigated whether ethanol consumption may lead to an increase in intestinal permeability to large molecules in patients with chronic alcohol abuse, using PEG with different sizes (Mr 400 - Mr 10.000). They showed that chronic alcohol consumption did lead to impairment of the intestinal barrier function and increased permeability to small and large molecules i.e., Mr 10,00032.

In contrast, the group of Hirsch *et al* 30 found no alteration in intestinal permeability in both chronic alcoholics and in healthy individuals, tested after three days of abstinence by a lactulose/mannitol ratio test30. Keshavarzian and co-workers investigated the effects of acute and chronic ethanol on the permeability of the gastric and small intestinal mucosa in alcoholics and healthy volunteers5. They concluded that chronic ethanol reversibly affects the integrity of small intestinal villi without significantly affecting gastrointestinal permeability. In contrast, a single oral dose of ethanol of 0.8g/kg increases gastroduodenal permeability but has no effect on the lactulose or mannitol permeability of the small intestine5.

Only two working groups reported on histological findings and concluded that no microscopic alterations of the gastrointestinal mucosa observed after administration of a single high dose of ethanol and chronic alcohol abuse5, 28. Millan *et al*. 31 investigated the effect of ethanol on the epithelial villi after intragastric alcohol administration. Biopsies were obtained at the peak of the blood alcohol concentrations and showed significant but transient damage to the villi of the upper small intestine31. Beside the controversial results of these histological studies, the mechanistic effects of alcohol on the TJs complex in human intestine have not yet been investigated.

In summary, although many in vitro and animal data clearly indicate that ethanol and its metabolite, acetaldehyde can affect intestinal permeability and epithelial integrity, human data are still limited and most of the studies have been performed in chronic alcohol abusers.

Many people of the general population consume low doses of ethanol on a regular basis and subgroup also incidentally consumes high doses. The effect of these drinking patterns on the intestinal permeability and TJs complex has not yet been studied.

The effect of alcohol on the intestinal permeability may have major consequences on health. It’s generally accepted that an increased intestinal permeability in alcoholic subjects lead to translocation of bacterial endotoxins from the gut lumen into the portal vein and then to the liver14. In the liver, endotoxins trigger the immune system and activate the resident macrophages, Kupffer cells. Activation of Kupffer cells leads to production of chemokines (IL-8) and proinflammatory cytokines (IL-1, TNFα), resulting in hepatocytes damage, inflammation, fibrosis and finally cirrhosis34.

Increased intestinal permeability has been also found in many gastrointestinal disorders such as celiac disease35, irritable bowel syndrome36, inflammatory bowel diseases35, 37.

Studying of these biological events is not only important for understanding the molecular mechanisms but also for the development of therapeutic agents, probably nutritional that are able to restore or prevent epithelial damage and the subsequent liver injury that may occur.

The aim of the present study is to investigate the effects of “moderate ethanol drinking” (2 drinks per day, equivalent to 20 g of ethanol) on the intestinal permeability and the tight junction complex. For that aim, blood and tissue samples from the proximal small intestine will be collected. A multi-sugar test will be applied to measure the intestinal permeability in healthy individuals.

The dose of ethanol will be based on an explorative study to assess the tolerability and the minimal effective dose to induce intestinal permeability changes as well as the correct timing for biopsy. Ethanol will be administered intraduodenally to overcome interindividual differences of oral, esophageal and gastric ADH activity and to avoid the possible dilution of ethanol by gastric secretions.

**Hypothesis and objectives**

**Hypothesis:**

Moderate ethanol intake increases intestinal permeability in the small intestine in healthy individuals and disrupts the tight junction complex.

**Primary outcome:**

- - To assess intestinal permeability by means of sugar permeability testing after intraduodenal administration of ethanol.

**Secondary outcome:**

- - To assess tight junctions structure and proteins in biopsy specimens after intraduodenal administration of ethanol.
  - To examine effects of ethanol and acetaldehyde on mucosal permeability in biopsy specimens in *ex vivo* circumstances using Ussing chamber methodology
  - To assess serum and mucosal ethanol and acetaldehyde concentrations after intraduodenal administration of ethanol.
  - To assess liver functions after ethanol administration i.e. AST, ALT and γGT.

If intestinal permeability is increased:

- To measure plasma endotoxin levels after ethanol administration.
- To assess serum inflammatory markers levels after ethanol administration.

**Aims of the explorative study:**

The aims of the explorative study are:

- To establish the minimal effective dose of ethanol required to induce increased intestinal permeability.
- To assess the safety and tolerability of the dose.
- To determine the peak of blood ethanol concentration.

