**Materials and methods**

**Study design**

**The explorative study**

Five male healthy volunteers will be included in the explorative study. Ethanol 20g will be administered as starting dose, using an intraduodenal catheter. The dose will be increased gradually (i.e 30 g maximum) if necessary. Permeability tests will be performed by a multi- sugar tests. (MEC 08-2-070, MEC 04-168).

[figure not shown]

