**Figure 3: Schematic diagram showing the design of the explorative study.**

Healthy subjects selected for the explorative study will be instructed to fast overnight from 22:00 PM and will be requested to arrive at the hospital endoscopy unit at 08.00 AM for blood sampling and insertion of the intraduodenal tube. The correct position of the tube will be checked by an X-ray. Once the tube is situated in the duodenum, 20 g of food grade ethanol (EtOH) diluted in tap water to 200 ml (i.e. final concentration of 10 %) will be infused within 15 minutes. Blood samples will be collected at t = -15 min, t = 15 min, t = 30 min, t = 45 min, t = 60 min, t = 120 min and t = 180 min (See figure 3). At t = 15 min, the sugar solution (5 g lactulose and 0.5 g L-rhamnose in 100 ml of tap water) will be ingested orally. Subjects will be requested to remain fasting and only water and tea without sugar will be allowed until the end of the study day. Urine samples will be collected during the first 5 hours.

The time of biopsy sampling for the definitive study will be determined by the peak of blood ethanol concentration.

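### The explorative study is asked for the lowest ethanol dose that raises permeability, but no control sugar test is described, so it cannot meet that aim

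*Protocol*

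**What the plan says.** Under Aims of the explorative study, the first of three aims is "To establish the minimal effective dose of ethanol required to induce increased intestinal permeability". The end of the Introduction repeats it: the dose is to rest on tolerability and on "the minimal effective dose to induce intestinal permeability changes". The other two aims are safety and tolerability, and the time of the blood ethanol peak, which sets the time of biopsy in the definitive study.

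The design is given in Materials and methods, The explorative study, and in the text under Figure 3:

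- "Five male healthy volunteers will be included in the explorative study".
- "Ethanol 20g will be administered as starting dose, using an intraduodenal catheter", and then "The dose will be increased gradually (i.e 30 g maximum) if necessary".
- "Blood samples will be collected at t = -15 min, t = 15 min, t = 30 min, t = 45 min, t = 60 min, t = 120 min and" finally at 180 min.
- "At t = 15 min, the sugar solution (5 g lactulose and 0.5 g L-rhamnose in 100 ml of tap water) will be ingested orally", with urine collected over the first five hours.

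These sections mention no water infusion, no sugar test before ethanol and no ethanol-free day. They do not say what would make a dose effective or an increase necessary. The Abstract (Interventions), the General considerations for the definitive study and the text under Figure 4 all take the definitive dose from this study. Only the definitive study has a placebo day.

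**The concern.** An increase is a contrast, and here it needs an ethanol-free reference in the same men. Every sugar ratio that the explorative study can produce comes after ethanol. The aim and the design meant to deliver it therefore do not fit together.

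The dose decision is what is at stake. If the sugar results are read as showing an effect, or no effect, they can only be read against a ratio from other people in other work. Escalation could then be triggered or withheld by spread between subjects. The definitive trial could report its dose as the lowest effective one without evidence for that description. The Introduction equates moderate drinking with 20 g, so a move up the range also changes how the result relates to the stated question.

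**Working it through.** **1. Which contrasts the explorative day allows.**

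- t = -15 min: before ethanol and before the sugars. The probes have not been given, so no baseline lactulose/rhamnose ratio exists.
- Ethanol is infused within 15 minutes, and the sugars are drunk at t = 15 min.
- All later blood samples, and the five-hour urine, follow ethanol.

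A change from no ethanol cannot be formed within a subject. If the same men go through more than one dose, a change between doses can be.

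**2. The plan's own figure.** Samples size gives a difference of 0.018, SD 0.02, alpha 0.05, power 80% and n = 12. I take the test as two-sided (not stated) and the SD as that of the paired differences. A paired t-test then has non-centrality (0.018/0.02) × √n. Power is 76.7% at n = 11 and 81.0% at n = 12, so 12 is reproduced. The explorative study has no stated size calculation.

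**3. The only reference available.** Samples size gives a baseline ratio of 0.013 (SD 0.009) from the earlier indomethacin work. For five men with no ethanol effect:

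- SE = 0.009/√5 = 0.0040.
- 95% half-width = 2.776 × 0.0040 = 0.011, which is 0.0112/0.013 = 86% of the baseline mean.
- P(mean exceeds 0.013 by 20% or more) = P(Z > 0.0026/0.0040) = P(Z > 0.65) = 26%.
- P(exceeds it by 30% or more) = P(Z > 0.0039/0.0040) = P(Z > 0.97) = 17%.

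These figures assume normality, treat 0.013 as exact, and allow nothing for differences in population or assay.

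**4. A large effect would be easier to see.** Take an illustrative cut-off half-way to the planning effect, 0.013 + 0.009 = 0.022.

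- With no effect (SD 0.009), the mean passes with probability P(Z > 0.009/0.0040) = P(Z > 2.24) = 1.3%.
- With the full planning effect (mean 0.031, SD 0.020, SE 0.020/√5 = 0.0089), it is missed with probability P(Z < -0.009/0.0089) = P(Z < -1.01) = 16%.

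**5. Comparing dose steps.** Suppose the same five men were tested at two doses, the true increment were 0.006 to 0.009 (one third to one half of 0.018; an assumption), and the SD of differences were 0.02. Power would be 8% to 12%.

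**6. What five men could show with a control day.** With a paired ethanol-free test, a difference of 0.018 and an SD of differences of 0.02, power is 33.9%. A one-sample comparison with a fixed historical value, using the same difference and SD, gives the same 33.9%. That figure measures the size of the group, not the lack of a control.

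**The case against.** Several points on the other side stand.

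- Figure 3 is not shown, and the General considerations for the explorative study speak of meals before each study day, so more than one day per man may be intended. Those days may be dose steps only. The text narrates the day in full without a control, so the fair statement is that none is described.
- A reader might infer that no within-subject change of any kind can be computed. That goes too far: a between-dose change is possible if the same men are escalated. It would not show an increase over no ethanol.
- A reader might infer that the definitive dose is chosen on noise. The document's own figures do not support that. An effect as large as indomethacin's would usually be visible against the old baseline (step 4), provided that baseline transfers. The dose is also bounded between 20 and 30 g, and tolerability informs it.
- A reader might cite the 34% power as the cost of having no control. It is the same after a control day is added, and the explorative study plans no significance test.
- No section says that the sugar results will be compared with the earlier baseline. That comparison is used here only because the document offers no other.

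None of this supplies the ethanol-free contrast that the first aim needs. Nor is this detail that a statistical analysis plan would normally settle, because the aim and the design conflict within the Protocol itself.

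**Conclusion.** The point holds in a limited form. The explorative study as described cannot establish the lowest dose that raises permeability, because it has no described ethanol-free sugar test. The one outside reference is too imprecise for a modest rise: half-width about 0.011 on a baseline of 0.013, and about a one in four chance of an apparent rise of 20% or more with no effect at all. These figures rest on normality, on the quoted baseline SD of 0.009, and on that baseline applying to these men and this assay.

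The other two explorative aims need no control and are unaffected. A reader might also infer that the definitive result is compromised. It is not: the randomised, placebo-controlled, paired comparison is valid at whatever dose is used. What is unsupported is describing that dose as minimally effective and tying escalation to a rise in permeability.

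**What to change.** Reconcile the eight places that bear on this: Abstract (Interventions); the end of the Introduction; Aims of the explorative study; the General considerations for each of the two studies; The explorative study; and the texts under Figures 3 and 4.

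1. Remove the aim of finding the lowest effective dose.
2. Limit the explorative study to what it can measure: safety and tolerability, the blood ethanol peak, and the biopsy time that follows from it.
3. State that its sugar results are descriptive only.
4. State the basis for the definitive dose, and for deciding that an increase is needed, in terms consistent with points 1 to 3.

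No dose or dose rule is proposed; that basis is for the sponsor to set. The cost is a protocol edit plus that decision. The downside is small: the Protocol can no longer claim that the dose was selected on permeability.

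Adding a water day for the five men is not recommended. It would mean another duodenal tube, X-ray and test day for each, with the alcohol-free week and standard meals beforehand. It would make an increase estimable, but with about 34% power for the planning effect it would still not establish a minimal effective dose.
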